#### Statistical analysis

Data analysis and reporting will follow the CONSORT guidelines for randomized controlled trials [68] and will be conducted according to the following principles. The trial statistician and researchers will be blinded to group status. No intermediate analysis is planned, as there is no added risk for women and neonates from this study compared with routine practices in France. Data will be analyzed by the intention-to-treat principle, i.e., all randomized participants will be analyzed according to their original allocation, regardless of protocol adherence. Baseline demographic and clinical characteristics of women, including adherence to the protocol, and outcomes will be described and compared by allocated treatment. Categorical variables will be summarized by numbers and percentages of patients in each treatment group and compared by Chi-2 or Fisher’s exact tests, as appropriate. Quantitative variables will be presented as means (standard deviations) if their distribution is normal and medians (interquartile ranges) otherwise; they will be compared with Student or Mann-Whitney-Wilcoxon tests, as appropriate. All these statistical tests will be two-sided and the level of statistical significance will be set at 5% (2-sided).

The effects of tocolysis will be expressed as relative risks with their 95% CIs for categorical outcomes and as mean differences with their 95% CIs for quantitative outcomes. Risk ratios and 95% CIs will be calculated for the primary outcome by using Poisson regression with a robust variance estimation, first unadjusted and then adjusted for minimization factors. Center will be fitted as a random effect, and the other minimization factors as fixed effects. The results will also be expressed as absolute risk differences with 95% CIs for binary outcomes. We will assess the Number Needed to Treat (NNT), defined as the number of patients who must be treated to prevent one additional adverse outcome.

Secondary outcome measures will be approached similarly to the primary outcome measure. Latency duration will be evaluated by Kaplan-Meier estimators and compared between the two treatment groups with the Log rank test and Cox proportional hazards regression, adjusted for gestational age at PPROM, if the proportional risks hypothesis is verified.

As a secondary analysis, we will analyze a per-protocol population, namely, women who received the full experimental treatment (eight tablets of nifedipine or placebo).

Characteristics of participants with and without missing data will be compared. If missing data are considered to be missing at random, we will perform multiple imputations with chained equations, with a logistic imputation model for binary covariates and a multinomial imputation model for categorical variables. Otherwise, participants with missing data will be excluded from analyses.

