#### Allocation of treatment

After the local investigator (an obstetrician or a midwife) has obtained maternal consent and immediately after inclusion in the trial, he or she will use a centralized procedure provided by a web-based computerized program with secure access (CleanWEB™ software) to randomize the patient. The randomization procedure will use minimization, a dynamic method that allocates subjects to the treatment group that best maintains balance in stratifying factors [49, 50]. Thus, the randomization list is not produced before the trial starts, but during participant recruitment. Minimization will be based on three prognostic factors: uterine contractions felt by the patient at the time of inclusion (presence or absence), recruiting center (1 to 29), and gestational age at PPROM (22/23 weeks, 24/26 weeks, 27/30 weeks, 31/33 weeks). The first 50 patients will be assigned through simple randomization. For the next step, the marginal totals in each treatment arm for the prognostic factors of the 51st patient will be calculated; the objective is to balance these marginal totals. The 51st patient will be assigned to the arm that improves the balance according to the preselected set of factors between the 2 trial arms. The same process will be applied for each new patient. 10% of randomness will be incorporated into the minimization algorithm, to make the prediction unlikely.

Each woman will receive a unique identification number after inclusion and a treatment box number after randomization.

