### Statistical issues

#### Sample size

Within the prospective, national, population-based EPIPAGE-2 cohort study of preterm births, we selected a sample of 888 women according to the TOCOPROM eligibility criteria and estimated the frequency of infants diagnosed with any criterion of the composite primary outcome to be 35.5%. This is an average estimate taking into account the expected variation of gestational age at birth in our study population from 22 to 37+ weeks. This estimate is consistent with findings in recent studies [15, 52, 66].

We hypothesized that the beneficial effect of tocolysis would be mediated by both higher gestational age at birth and the administration of a complete course of antenatal corticosteroids. The EPIPAGE-2 study showed that among women with PPROM, each one-day increase in gestational age at birth is significantly associated with a reduced relative risk (RR) of fetal or neonatal death or severe morbidity (RR 0.95, 95% CI 0.91–0.99) [10]. With pregnancy prolonged by 48 h by effective tocolysis, we expect to reduce the rate of fetal or neonatal death or severe morbidity by 10%. Each additional day after the initial 48-h period will also contribute to reducing adverse outcomes. Moreover, this initial prolongation will allow a complete course of antenatal corticosteroids, with additional beneficial effects, as shown by Roberts et al. [28, 67]. In meta-analyses of women with PPROM, antenatal steroids have been associated with reduced perinatal (RR 0.59, 95%CI 0.39–0.90) and neonatal mortality (RR 0.61, 0.46-0.83), respiratory distress syndrome (RR 0.70, 0.55-0.90), chronic lung disease (RR 0.50, 0.33–0.76), necrotizing enterocolitis (RR 0.39, 0.18–0.86), and IVH (RR 0.47, 0.28-0.79). Retinopathy of prematurity, early-onset sepsis, and periventricular leukomalacia were not analyzed separately by membrane status in these meta-analyses.

When we assume an alpha-risk of 0.05 and a beta-risk of 0.20 (i.e., statistical power of 80%), 702 women (351 per arm) are required to show a reduction of the primary endpoint from 35% (placebo group) to 25% (nifedipine group). We plan to increase the required number of subjects by 20%, to replace patients who leave the study early. The total number of subjects required is thus 850.

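### The primary outcome gets an unadjusted and a minimization-adjusted risk ratio with neither named as decisive; the unadjusted one is conservative under this allocation, so the adjusted model should decide

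*Protocol article*

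**What the plan says.** Under Allocation of treatment: "Minimization will be based on three prognostic factors". These are contractions felt at inclusion (yes or no), recruiting center (29) and gestational age at PPROM (four bands). The first 50 women are allocated by simple randomization; after that the arm that improves marginal balance is chosen, with 10% randomness.

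Under Statistical analysis there is first a general rule for baseline characteristics and outcomes: "Categorical variables will be summarized by numbers and percentages of patients in each treatment group and compared by Chi-2" or Fisher's exact test. It closes with "All these statistical tests will be two-sided and the level of statistical significance will be set at 5% (2-sided)". The primary outcome then has its own sentence, giving risk ratios with 95% intervals from Poisson regression with robust variance, "first unadjusted and then adjusted for minimization factors". In the adjusted model, center is a random effect and the other minimization factors are fixed effects. Absolute risk differences and a number needed to treat are also promised, without naming the model that supplies them. Nothing in the section says which risk ratio, interval and p-value the conclusion rests on.

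**The concern.** Minimization makes the arms more alike on its factors than chance would. If a factor predicts the outcome, the true sampling variance of the arm comparison falls. A Chi-2 test or an unadjusted risk ratio does not see this: its standard error still includes the between-band variance that the allocation has removed. The interval is then too wide and the test rejects less often than its nominal 5%.

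The article gives reason to expect a strong factor. Its Background says that the infant's prognosis depends mainly on gestational age at birth, and that 50 to 60% of women deliver within a week of PPROM. Gestational age at PPROM, which is balanced, should therefore carry much of that information.

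At stake are precision and power that the design has already paid for, and a determinate conclusion. With two models and no stated priority, a result near 0.05 could be read either way.

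**Working it through.** **1. The plan's own figure.** Inputs from Sample size: "reduction of the primary endpoint from 35% (placebo group) to 25% (nifedipine group"), two-sided 5%, 80% power. Pooled two-proportion formula per arm: [1.960 × √(2 × 0.30 × 0.70) + 0.842 × √(0.35 × 0.65 + 0.25 × 0.75)]² / 0.10² = 1.812² / 0.01 = 328.5, so 329. With continuity correction: (328.5/4) × [1 + √(1 + 4/(328.5 × 0.10))]² = 348.2, so 349. The article states "702 women (351 per arm) are required to show a reduction". The figure is therefore reproduced closely by the continuity-corrected formula, which is an unadjusted test.

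**2. Assumptions.** The article gives neither the share of women nor the risk in each gestational-age band (22/23, 24/26, 27/30, 31/33 weeks). Two sets are used, each with a steep and a flatter gradient and an overall risk of 35% to 36%:
- Set A: shares 8/17/35/40%; risks 85/70/35/12% (steep) or 65/50/36/24% (flatter).
- Set B: shares 8/22/35/35%; risks 85/62/32/9.7% (steep) or 60/48/34/22% (flatter).

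**3. Closed-form check, taking perfect balance on the bands.** The unadjusted standard error uses p̄(1 − p̄), while the true variance follows Σ share × p(1 − p). The inflation factor is k = √(total/within), and the actual type I error is 2 × P(Z > 1.96k).

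| Scenario | Within | Total | Ratio | k | Type I error |
|---|---|---|---|---|---|
| A steep | 0.1678 | 0.2297 | 0.73 | 1.17 | 2.2% |
| A flatter | 0.2143 | 0.2301 | 0.93 | 1.04 | 4.2% |
| B steep | 0.1688 | 0.2276 | 0.74 | 1.16 | 2.3% |
| B flatter | 0.2127 | 0.2274 | 0.94 | 1.03 | 4.3% |

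**4. Simulation of the stated minimization.** N = 702; Poisson with robust variance; adjusted for gestational-age band and contractions. The center random effect was not fitted. Set B used 4,000 trials per scenario and set A 2,000.

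| Quantity (unadjusted v adjusted) | B steep | B flatter | A steep | A flatter |
|---|---|---|---|---|
| Type I error | 2.5% v 5.2% | 4.0% v 4.9% | 3.0% v 5.5% | 4.4% v 5.2% |
| Power at RR 25/35 = 0.714 | 84.2% v 89.6% | 83.3% v 84.5% | 87% v 91% | – |
| Power at RR 0.80 | – | – | 52% v 63% | 50% v 53% |

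Chi-2 follows the unadjusted model: type I error 2.6% and 4.1%, and power 84.6% and 83.5%, in set B.

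Standard error of the log risk ratio under no effect, set B steep: unadjusted 0.1034 against a true SD of 0.0901, ratio 1.15; adjusted 0.0890 against 0.0899. Set B flatter: 0.1033 against 0.0999, ratio 1.03; adjusted 0.0996 against 0.0998.

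**5. Control.** Under simple randomization with the steep set B risks, the unadjusted standard error is right (0.1037 against 0.1048) and type I error is 5.0%. The miscalibration therefore comes from the forced balance. Monte Carlo error on a 5% rate with 4,000 trials is √(0.05 × 0.95/4000) = 0.34 points, so in the flatter case the standard-error ratio is better evidence than the type I error.

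**6. Repeat runs.** Further runs under the same kinds of assumption widen the ranges slightly: the unadjusted interval is 2% to 17% too wide, type I error is about 2% to 4.4%, and the power loss is 1 to 6 points at RR 0.714 and 2 to 12 points at RR 0.80. The two models fell on opposite sides of 0.05 in roughly 1% to 12% of trials with a real effect.

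**The case against.** The strongest reply is that the right model is already in the plan and only the word primary is missing. The Ethics section also says that a statistical plan was written before the trial started; it is not shown and may rank the analyses. Both points are fair. Placing the unadjusted result first sets an order of reporting and does not make it decisive, and a post-hoc choice is not established. What stands is that the article specifies the primary analysis down to the variance estimator and the random effect, yet includes an unadjusted analysis that its own allocation makes miscalibrated, and gives neither analysis precedence.

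A reader might infer more than this. The documents do not support the following:
- **Several p-values inflate false positives.** When any significant result among Chi-2, unadjusted and adjusted was counted, simulated type I error stayed between about 4.2% and 5.7%, essentially the adjusted model's own rate. Chi-2 and unadjusted Poisson disagreed in at most 0.35% of trials, so there are in effect two tests. The Chi-2 sentence is also generic.
- **The trial is underpowered for this reason.** At 35% v 25% the unadjusted analysis exceeds 80% power even at 702, and the article adds: "The total number of subjects required is thus 850".
- **Chi-2 gives over-wide intervals.** It gives none; that point concerns the unadjusted risk ratio only.

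Two limits also stand. The article's statement on prognosis concerns age at birth, and it describes latency from hours to several weeks, so the gradient by age at PPROM is uncertain. And the planned center random effect was not simulated.

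**Conclusion.** The point holds as a free improvement, not as a flaw that threatens validity. Under the stated minimization the unadjusted analyses err on the conservative side, while the adjusted model holds close to 5% and its standard error matches the true variation.

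The direction follows from the design. The size depends on risks and shares by gestational-age band that the article does not give: near the lower ends of the ranges if the gradient is flat, near the upper ends if it is steep. The risk ratio of 0.80 is also an assumption and not a stated target. A smaller effect than planned is nevertheless worth considering, because Sample size attributes only a 10% reduction to the 48-hour prolongation itself and relies on further days and steroids for the rest.

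The consequence is lost precision and a conclusion that is not fully determined in advance.

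**What to change.** Add a sentence to Statistical analysis saying that the Poisson model with robust variance, adjusted for the minimization factors as already specified, is the single primary analysis, and that its risk ratio, 95% interval and p-value are the basis for the conclusion. Label the unadjusted risk ratio and the Chi-2 test as supportive. State that the risk difference and number needed to treat are derived from the same adjusted model, for example by standardization. If the separate statistical plan already says this, bring the two texts into line.

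The cost is a few words: no extra women, data or time. To be credible it must be fixed before unblinding. Modelling gestational age continuously or with a spline is optional and not needed for this point.

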### Study intervention

The intervention will be the oral administration of either nifedipine 20 mg or placebo of nifedipine 20 mg (according to the randomization group) for 48 h according to the following administration protocol:
Loading dose: 1 tablet at Time 0 (T0) and T0.5 (i.e., 30 min after the first intake),Maintenance dose: 1 tablet at T3, T11, T19, T27, T35, and T43.

The total treatment duration will be 48 h, with nifedipine total doses of 100 mg on day 1 and 60 mg on day 2.

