#### Treatment administration

The allocated treatment box, containing 8 tablets of nifedipine or placebo, will be immediately given to the patient by the local investigator or by his/her delegate, along with a patient compliance form specifying the theoretical timing of each drug intake. The patient will start the protocol as soon as possible with the first intake. Within the first hour after starting nifedipine or placebo, blood pressure, heart rate, and clinical symptoms (such as dyspnea or thoracic pain) will be measured according to each maternity unit’s usual practices. Treatment will continue as long as blood pressure remains within normal limits, with blood pressure and heart rate thereafter measured 2 to 3 times per day. Clinical surveillance and management during the protocol will take place according to local practices, without any additional procedures or data collection. The treatment can be interrupted by the patient and/or the investigator for any reason deemed necessary (including the need for rescue tocolysis).

After each intake, the patient will report its actual date and time on the compliance form, as well as any side effects and comments. After the protocol is completed, the local investigator will collect the treatment box and blister pack and send them to the local pharmacy.

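### The per-protocol set requires all eight tablets, so it excludes fully adherent women who deliver before hour 43 and selects on early delivery, which tocolysis is meant to delay

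*Protocol article*

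**What the plan says.** Under Statistical analysis, the primary approach is intention to treat: "all randomized participants will be analyzed according to their original allocation, regardless of protocol adherence". The same section then adds: "As a secondary analysis, we will analyze a per-protocol population". It defines that population as "women who received the full experimental treatment (eight tablets of nifedipine or placebo".

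Under Study intervention, the tablet times are "Loading dose: 1 tablet at Time 0 (T0) and T0.5", then "Maintenance dose: 1 tablet at T3, T11, T19, T27, T35, and T43". Under Treatment administration, the supply matches: "The allocated treatment box, containing 8 tablets of nifedipine or placebo". The same section lets treatment end early: "The treatment can be interrupted by the patient and/or the investigator for any reason deemed necessary (including the need for rescue tocolysis". It also makes continuation depend on blood pressure staying within normal limits.

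No section says how a woman who delivers during the 48-hour course is to be classified for the per-protocol set.

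**The concern.** A per-protocol set should remove women who departed from the protocol. This one also removes women who followed it exactly until they gave birth, because their remaining tablets never fell due.

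Delivery before hour 43 is not a neutral reason for exclusion. The Background says tocolysis is meant to prolong pregnancy. The Sample size section says the expected benefit runs through higher gestational age at birth and a complete steroid course, and attaches a 10% reduction in the outcome to 48 hours of prolongation. Secondary outcome measures lists prolongation beyond 48 h as an outcome. The set is therefore chosen on a post-randomization event that treatment is expected to change. If nifedipine does delay delivery, its arm keeps women whose counterparts on placebo delivered and were dropped, and the two retained groups are no longer comparable.

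At stake is a pre-specified secondary relative risk that could differ from the intention-to-treat result for reasons unrelated to adherence. The article does not restrict the analysis to the primary outcome. If it is applied to prolongation beyond 48 h, nearly every retained woman has the outcome by construction.

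**Working it through.** **1. Schedule.** Intakes fall at hours 0, 0.5, 3, 11, 19, 27, 35 and 43, which makes eight. Five fall before hour 24 (5 × 20 = 100 mg) and three after (3 × 20 = 60 mg). This reproduces the stated daily totals: "with nifedipine total doses of 100 mg on day 1 and 60 mg on day 2". On schedule, a woman delivering at hour 30 has taken six tablets, and one delivering just before hour 43 has taken seven. Both fail the definition.

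**2. Share excluded by delivery alone.** The article gives no figure for 43 hours. Its Background gives 50-60% delivering within one week (168 h) of rupture. Assuming a constant hazard:
- 1 − (1 − 0.50)^(43/168) = 0.163
- 1 − (1 − 0.60)^(43/168) = 0.209

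That is roughly 16-21%. The true share would be higher if the hazard is concentrated in the first days.

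**3. Effect on the relative risk (RR).** Notation:
- e0, e1: share delivering before hour 43 on placebo and on nifedipine
- rE: outcome risk of early deliverers
- rL: outcome risk of women who would pass hour 43 on either arm
- rS: risk, on nifedipine, of women who pass hour 43 only because of nifedipine

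Suppose delivery is the only reason for an incomplete course, and nifedipine changes nothing for women who would pass hour 43 on either arm. Then:
- Intention to treat (ITT), placebo = e0·rE + (1 − e0)·rL
- ITT, nifedipine = e1·rE + (e0 − e1)·rS + (1 − e0)·rL
- Per-protocol (PP), placebo = rL
- PP, nifedipine = [(e0 − e1)·rS + (1 − e0)·rL] / (1 − e1)

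Assumed inputs: e0 = 0.30, e1 = 0.20, rE = 0.50. The placebo risk of 35% is the article's, so rL = (0.35 − 0.15)/0.70 = 0.286.

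| Postponed women's risk rS | ITT RR | PP RR |
|---|---|---|
| 0.286 (falls to late-delivery risk) | 0.329/0.35 = 0.94 | 0.286/0.286 = 1.00 |
| 0.40 (falls part of the way) | 0.34/0.35 = 0.97 | 0.300/0.286 = 1.05 |
| 0.50 (delay brings no benefit) | 0.35/0.35 = 1.00 | 0.3125/0.286 = 1.09 |

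The first row does not depend on the inputs: when rS = rL, the per-protocol nifedipine risk reduces to rL, so the RR is exactly 1.00.

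**4. Same early-delivery inputs, with the design effect imposed.** The Sample size section assumes 35% v 25%, an ITT RR of 0.25/0.35 = 0.71. Keep early delivery at 30% v 20% and early risk at 50% in both arms, and solve for the late risk:
- Placebo: (0.35 − 0.30 × 0.50)/0.70 = 0.286
- Nifedipine: (0.25 − 0.20 × 0.50)/0.80 = 0.1875
- PP RR = 0.1875/0.286 = 0.66

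With 20% v 13% early delivery, the late risks are 0.25/0.80 = 0.3125 and 0.185/0.87 = 0.213, and the PP RR is 0.68.

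**5. Why steps 3 and 4 differ.** Step 3 cannot reach the design effect. Even with rS = 0, the ITT nifedipine risk is 0.10 + 0 + 0.20 = 0.30, not 0.25. A 25% risk requires benefit among women who would complete the course on either arm, which step 3 rules out by assumption.

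**The case against.** The strongest reply is that little rests on this analysis. The trial is a superiority trial, the article makes intention to treat the governing principle, and the per-protocol set is one sentence labelled secondary. No success criterion depends on it. That stands, and it limits the weight of the point.

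A reader might infer that the rule would erase or reverse a true benefit. The article does not support this as a general statement. The results in step 3 assume no benefit in women who complete the course on either arm, whereas the Sample size section expects each further day after the first 48 hours to help as well. Under the article's own design effect, the per-protocol RR moves the other way, to about 0.66 against 0.71.

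A reader might also suppose that stops for low blood pressure fall mainly on nifedipine and rescue tocolysis mainly on placebo. Both are plausible, but the article gives no frequencies by arm. Nor does the rule remove only adherent women, since it also removes those who missed tablets or stopped early, as a per-protocol rule should.

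Finally, the article already plans to describe and compare adherence by arm. That helps interpretation but does not change who is in the set. None of these replies answers the definitional point: the all-eight-tablets rule is stated as a definition, and it treats delivery as non-adherence.

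**Conclusion.** The point holds for the definition of one secondary analysis. The exclusion of adherent women who deliver before hour 43 follows from the article's text and schedule and needs no assumption. Hour 43 runs from first intake, which is to follow randomization as soon as possible.

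The size and direction of the resulting bias are not determined. The illustrations run from 0.66 against an ITT RR of 0.71, through 1.00 against 0.94, to 1.09 against 1.00. All rest on assumed early-delivery shares and early risk. The 16-21% excluded by delivery is likewise an assumption-based estimate, not a figure from the article. The variable selected on is early delivery, a presumed mediator and a secondary outcome; it is not the primary composite itself. A reader should not infer that the trial's main result is compromised: the intention-to-treat analysis and the sample size of 702, raised to 850, are untouched.

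**What to change.** Define the per-protocol population as eligible women who took every tablet that fell due before delivery, judged from compliance-form times against delivery time, so that delivery never counts as non-adherence. Report reasons for incomplete courses by arm. Describe the analysis as a supportive, non-randomized comparison.

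The cost is mainly wording. The compliance form already records the actual date and time of each intake, with side effects and comments, and delivery time is needed for latency. If reasons for stopping are not coded, they would have to be drawn from those comments or the medical file.

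There are two downsides. The set will include women with short exposure, some with only one or two tablets. Selection from stops for side effects or rescue tocolysis remains, so the revised comparison is less distorted but still not protected by randomization.

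### The missing-data rule rests on a judgement the data cannot settle, and its fallback drops randomized participants where dropping them is hardest to defend

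*Protocol article*

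**What the plan says.** The end of the Statistical analysis section of the protocol article sets out three steps.

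- First, a description: "Characteristics of participants with and without missing data will be compared".
- Then a condition: "If missing data are considered to be missing at random, we will perform multiple imputations with chained equations".
- Then the fallback: "Otherwise, participants with missing data will be excluded from analyses".

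The fallback is not limited to any outcome, so it reaches the primary composite. Earlier in the same section, intention to treat is defined as "all randomized participants will be analyzed according to their original allocation, regardless of protocol adherence".

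The Sample size section allows for losses: "We plan to increase the required number of subjects by 20%, to replace patients who leave the study early".

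**The concern.** There are three difficulties.

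1. **The check cannot answer the question.** Comparing participants with and without missing data can give evidence against missing completely at random (MCAR). MAR and MNAR differ only in how missingness relates to the unobserved values, so no comparison of observed characteristics separates them. A difference in observed characteristics is also the situation in which imputing from those characteristics helps most; under this rule it could be taken as a reason to delete.
2. **The fallback does not fit the problem.** Apart from MCAR, the branch is reached when MNAR is suspected. Complete-case analysis is then generally biased and does nothing about the mechanism.
3. **Two statements collide.** If the branch is taken, participants with missing data leave the analysis, although the section says that all randomized participants are analyzed.

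At stake is the primary RR. Its analysis set would depend on a judgement made after the data are in, and loss related to the infant's condition could move the estimate either way. The 2-year outcomes are more exposed, because they come from a questionnaire that parents complete (Child follow-up).

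**Working it through.** **The plan's own figures.** The documents give no missing-data rate, so there is no missing-data figure to reproduce. The design inputs do reproduce closely: 35% against 25%, two-sided 5%, 80% power, 1:1. Without continuity correction:

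n = [1.96·√(2·0.30·0.70) + 0.8416·√(0.35·0.65 + 0.25·0.75)]² / 0.10² ≈ 329 per arm.

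With continuity correction: (329/4)·[1 + √(1 + 4/(329·0.10))]² ≈ 349 per arm (698 in total), against the stated 351 (702). Then 702 × 1.2 = 842, which the plan states as 850, or 425 per arm.

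**Bias of exclusion, simplest form.** Let p be the true risk, m the fraction missing and q the event risk among the missing. The complete-case risk is (p − m·q)/(1 − m). Assume no true effect (p = 0.35 in both arms) and outcome-independent loss on placebo, which leaves that arm at 35%. All values of m and q are assumptions.

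- Nifedipine m = 0.10, q = 0.60: (0.35 − 0.060)/0.90 = 0.322; RR = 0.322/0.35 = 0.92.
- Nifedipine m = 0.02, q = 0.60: (0.35 − 0.012)/0.98 = 0.345; RR = 0.985.

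**Direction, and the role of a difference between arms.** Let a be the fraction of events missing and b the fraction of non-events missing in an arm. The complete-case risk is p(1−a)/[p(1−a) + (1−p)(1−b)]. Rejection is the two-sided 5% normal-approximation test starting from 425 per arm. The truth is 35% in both arms.

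| Assumed loss | Nifedipine arm missing | Complete-case risk, placebo / nifedipine | RR (truth 1.00) | Rejection |
|---|---|---|---|---|
| Nifedipine only: a = 10%, b = 0 | 3.5% | 35.0% / 32.6% | 0.93 | 11% |
| Nifedipine only: a = 20%, b = 0 | 7.0% | 35.0% / 30.1% | 0.86 | 32% |
| Nifedipine only: a = 5%, b = 20% | 14.75% | 35.0% / 39.0% | 1.11 | 21% |
| Both arms: a = 20%, b = 5% | 10.25% | 31.2% / 31.2% | 1.00 | 5% |

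Under the design effect (0.25/0.35 = 0.714), the four patterns give RR 0.66, 0.60, 0.81 and 0.70. In the third, power falls from 89% with complete data to 51%.

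**Bounds that assume no mechanism.** If the observed risks are 35% and 25% and a fraction m is missing in each arm, the full-cohort risk difference lies within −0.10(1 − m) ± m:

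- m = 2%: −11.8 to −7.8 points
- m = 5%: −14.5 to −4.5 points
- m = 10%: −19.0 to +1.0 points

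**The case against.** **Primary-outcome loss may be small.** The endpoint is assessed in hospital and taken from medical files. Under Data collection, management, and monitoring, records are requested when delivery or neonatal care takes place elsewhere, and the primary outcome is monitored on site. This stands. Nothing in the document shows material missingness in the primary outcome.

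**Loss that differs by arm is harder to assume in a double-blind trial** with identical boxes. This also stands as a limit on size: with the same mechanism in both arms, the null RR stays at 1.00.

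**The statistician is blinded to group status.** That limits steering the choice of branch by the treatment effect. It does not make the check informative or the fallback unbiased.

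**The word for otherwise also covers MCAR,** where exclusion is unbiased and only loses precision. Correct; the criticism concerns the MNAR case. The text also does not say that the comparison of characteristics is the sole criterion, only that it is the one named.

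**The details belong to the analysis plan,** which is not shown. This holds for imputation predictors and sensitivity runs, whose absence here is no finding. It does not hold for the exclusion rule, which the article itself states.

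Two stronger readings are tempting. A reader might infer that the primary result will be biased. The document does not support that, since the branch may never be taken and the loss may be small or alike in both arms. A reader might also take the 20% allowance as the expected share of missing outcomes. It is an inflation to replace women who leave early, and says nothing about how many infants will lack an in-hospital outcome.

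**Conclusion.** The rule is wrong as written. It makes the analysis set depend on a distinction that the named check cannot draw. Outside MCAR, it answers suspected MNAR with a method that does not address it. It also cannot be reconciled with analyzing all randomized participants.

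The consequence is conditional: a risk of bias of unknown size and direction if the exclusion branch is used. Under assumed loss patterns with no true effect, the RR ranges from 0.86 to 1.11 when outcome-dependent loss differs by arm. It is about 0.985 at 2% missing on nifedipine with 60% events among them, and 1.00 when the mechanism is the same in both arms. These rest on assumed missingness, because the document gives none. The sample size calculation is not affected.

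**What to change.** - Delete the condition on MAR and the sentence that excludes participants otherwise.
- Prespecify one primary approach that retains all randomized women: multiple imputation under MAR, with arm, outcome and minimization factors in the imputation model.
- Address MNAR with delta-adjusted or tipping-point sensitivity analyses that vary the event risk of missing infants separately by arm. This part is needed because imputation under MAR does not itself remove MNAR bias.
- Keep complete-case analysis as supportive only. The comparison of characteristics can stay as description, but should not select the method.
- Apply the same rule to the 2-year outcomes.

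The cost is a change of wording and a little extra analysis. No new data are needed and the sample size is unchanged. The change should be dated before unblinding.
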